## 9.2 Planned Interim Analyses

As this is a strategy study that enrolls hospitals, there will be no planned interim analyses for safety in this protocol. We expect to summarize historical data while the prospective portion of the study is ongoing.

## 9.3 Participant Enrollment and Follow-Up

Data from participants admitted to the four hospitals during each of the two six month strategy periods are entered into the database. The data from admission until death or discharge are collected.

## 9.4 Analysis Plan

### 9.4.1 Analysis

#### 9.4.1.1 Primary feasibility summaries

The primary analyses will be descriptive (a summary as to whether each hospital was able to successfully implement each of the interventions). No hypothesis testing will be completed for these analyses.

#### 9.4.1.2 Secondary analyses

The analyses of the secondary objectives will consist of multiple analyses to address the hypotheses. The endpoints required for these analyses include, but are not limited to:

- Days of targeted and alternative antimicrobial use
- Prescriptions for targeted and alternative antimicrobials
- Days in hospital
- Death
- ICU admission
- Survey of provider perceptions
- Costs including cost of pharmacist and antimicrobial costs

#### 9.4.1.3 Discussion of cluster randomized design and the key secondary analysis

This antimicrobial stewardship study will be implemented at four hospitals, where each hospital is considered a single cluster. The four hospitals participating in this study will be paired by size. One hospital in each pair will receive Strategy 1 followed by Strategy 2, while the other hospital in each pair will receive Strategy 2 followed by Strategy 1. The ordering within each pair will be randomly assigned.

Cluster randomized trials can be analyzed at the cluster level or the patient level. Ideally, analyses are conducted on the cluster level as this is the unit of randomization. However, we will analyze this study using the patient as the unit of analyses as there are only four clusters.

Since randomization occurs at the cluster level but analyses must be conducted at the patient level, the benefits of randomization (i.e., expectation of balance of confounding factors) cannot be assumed. The small sample size of 4 clusters may also negate the benefits of randomization. The crossover nature of the design will help to balance confounding factors as each hospital can serve as its own control. However, as the crossover occurs at the cluster level, and the patients are neither randomized nor crossed-over, it does not have the same advantages as a standard crossover trial and it does not eliminate within-patient variation; the analyses cannot be “paired”.

Since the effect of the intervention is not only a function of the intervention itself but also of the pharmacist, there is potential for considerable site variation in response. Thus each of the four sites will be evaluated separately. Stratified pooled analyses may also be conducted.

For each site and each contrast (Intervention 1 vs. control; Intervention 2 vs. control; and Intervention 1 vs. Intervention 2), the difference in outcomes will be estimated using 95% confidence intervals. Examples for binary and continuous outcomes are displayed in Figure 9-2 and Figure 9-3, respectively.

Figure 9-2

### 95% CI for Difference in Proportions (Intervention 1 – Intervention 2)

[figure not shown]

Figure 9-3

[figure not shown]

Site heterogeneity of treatment effects will be explored by modeling outcome as a function of treatment, period, site, and period\*site interaction. Age, sex, and race will also be included to control for confounding by demographic variables. Treatment and period effects will be fixed. Site and period\*site effects will be random.

Exploratory analyses of the overall benefits and risks of the AS interventions will also be conducted using methods that are currently being developed.

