## 3.5 General statistical considerations

- Tables will be presented by Hospital and intervention; each of the 4 sites will be evaluated separately.
  - Stratified pooled analyses may also be conducted
- Dates will not be shown, but converted to days from intervention (intervention) or first hospital contact (feasibility).
- Each Table/Figure/Listing will be annotated with the name and location of the program used to create it, including its location directory.
- All programs that create permanent study-specific derived datasets or that contribute to analyses of the primary or secondary objectives will be validated according to CBAR SOPs
- Categorical variables will be summarized with n and proportion
- Continuous variables will be summarized with mean, sd, median, Q1, Q3, min and max.
- For secondary analyses, there are 3 contrasts of interest
  - PAR vs. historical control
  - Formulary Restriction/Preauthorization (Res/PreA) vs historical control
  - PAR vs Res/PreA
- For each contrast, the difference in outcomes will be estimated using 95% confidence intervals
  - Difference in proportion with 95% CIs for binary outcomes
  - Difference in means with 95% CIs for continuous outcomes

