### 3.5.1 Cluster Randomization and Analysis

This antimicrobial stewardship study was implemented at four hospitals, where each hospital is considered a single cluster. Cluster randomized trials can be analyzed at the cluster level or the patient level. Ideally, analyses are conducted on the cluster level as this is the unit of randomization. However, we will analyze this study using the patient as the unit of analyses as there are only four clusters.

Since randomization occurs at the cluster level but analyses must be conducted at the patient level, the benefits of randomization (i.e., expectation of balance of confounding factors) cannot be assumed. The small sample size of 4 clusters may also negate the benefits of randomization. The crossover nature of the design will help to balance confounding factors as each hospital can serve as its own control. However, as the crossover occurs at the cluster level, and the patients are neither randomized nor crossed-over, it does not have the same advantages as a standard crossover trial and it does not eliminate within-patient variation; the analyses cannot be “paired”.

Since the effect of the intervention is not only a function of the intervention itself but also of the pharmacist, there is potential for considerable site variation in response. Thus each of the four sites will be evaluated separately. Stratified pooled analyses may also be conducted.

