  - Admissions where the antibiotic was not received will have a DOT of 0.
- Modeling (1 model for each of the antibiotics of interest)
  - The purpose of the model is to look at the effect of the intervention on DOT for each antibiotic of interest
  - Dependent variable = DOT for each antibiotic
  - Adjusting for hospital, study period, AS strategy, calendar time, demographic variables
  - The interactions of study period \* strategy, hospital \* study period, hospital \* strategy, will be explored.

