#### **13. Patient specific outcomes between each strategy**

**Purpose:** to address secondary objective 3, to compare patient-specific outcomes between each strategy, including but not limited to the following:

494 a. Total hospital days

495 b. Intensive care unit admission

496 Each of Total hospital days, death, and ICU admission will be summarized by hospital in 3 tables:

497 Among admissions with an included antibiotic

498 • Table 1

499 ○ Year prior to study

500 ○ Period 1 Admission with Included antibiotic, no intervention

501 ○ Period 1 Admission with stewardship intervention

502 ○ Period 2 admission with Included antibiotic, no intervention

503 ○ Period 2 admission with stewardship intervention

504 • Table 2

505 ○ Period 1 (all admissions with an antibiotic of interest)

506 ○ Period 2 (all admissions with an antibiotic of interest)

507 • Table 3

508 ○ For 3 contrasts (PAR vs Historical year; Res/PreA vs historical Year; PAR vs Res/PreA)

509 ○ Difference in proportion of ICU admissions with 95%CI

510 ○ Difference in Mean total hospital days with 95% CI

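### No model adjusts for case-mix beyond demographics, and SAP section 13 gives only crude differences, so case-mix shifts enter the site-specific and historical contrasts

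*Combined protocol and SAP*

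**What the plan says.** Protocol section 9.4.1.3 sets out one generic model: "Site heterogeneity of treatment effects will be explored by modeling outcome as a function of treatment, period, site, and period\*site interaction". Treatment and period are fixed; site and its interaction with period are random. The patient-level covariates follow: "Age, sex, and race will also be included to control for confounding by demographic variables".

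SAP section 10 has one model per antibiotic for DOT: "Adjusting for hospital, study period, AS strategy, calendar time, demographic variables". The demographic variables are not itemised, and no diagnosis, comorbidity or severity term appears.

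SAP section 13 covers hospital days, death and ICU admission through three tables and no model. Table 3 lists "Difference in proportion of ICU admissions with 95%CI" and "Difference in Mean total hospital days with 95% CI". Death is to be summarised but has no line in Table 3. SAP section 3.5 describes contrasts the same way: "For each contrast, the difference in outcomes will be estimated using 95% confidence intervals".

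On confounding, SAP section 3.5.1 says that "the benefits of randomization (i.e., expectation of balance of confounding factors) cannot be assumed". On presentation it says: "Thus each of the four sites will be evaluated separately. Stratified pooled analyses may also be conducted".

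Protocol sections 5.1 and 16.2 list the routine files received: pharmacy, admission-discharge-transfer (ADT), bed flow, demographics, billing ICD-9 and microbiology. No case-mix variable is derived from any of them for adjustment, and SAP section 8 describes patients by demographics and body size only.

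**The concern.** The plan states that patient-level balance cannot be relied on, then controls only for demographics, and in SAP section 13 for nothing. The SAP does not say whether the protocol's outcome model applies to hospital days, ICU admission and death.

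At each hospital one strategy runs from October to early April and the other from May to late October (SAP section 6). Within a hospital, strategy and period are the same variable, so a period term cannot separate them. If sicker patients are admitted in one period, the crude contrast attributes their longer stays and ICU use to the strategy. The same applies to each strategy against the historical year, for which protocol section 4 says seasonal and temporal effects are not controlled.

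At stake are stated secondary outcomes, and results that protocol section 10 intends to use in planning a larger trial.

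**Working it through.** **1. The plan's own figure.** Protocol section 9.1 gives 97% power for 0.50 against a 0.05 difference, 3,000 patients per period, alpha 0.05. Two-sided, with 0.45 in the other group:

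- null SE = √(2 × 0.475 × 0.525 / 3000) = 0.01289
- alternative SE = √((0.50 × 0.50 + 0.45 × 0.55) / 3000) = 0.01288
- power = Φ((0.05 − 1.96 × 0.01289) / 0.01288) = Φ(1.92) = 97.3%

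The figure reproduces. It describes sampling error only and does not bear on bias.

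**2. Where a shift goes.** Two hospitals run each order. Take the contrast as Strategy 1 minus Strategy 2, and let case-mix alone move an outcome by +1 point from period 1 to period 2, with no strategy effect.

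| Shift | Site-specific contrasts | Pooled, equal weights |
|---|---|---|
| Same at all four hospitals | −1, +1, +1, −1 | 0 |
| At one hospital only | 1 in size there, 0 elsewhere | 0.25 in size |
| Opposite in the two orders | 1 in size, same sign at all four | 1 in size |

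Site-specific contrasts carry the shift in full. Pooling removes only the common part. A shift between the control year and the study year does not cancel in the historical contrasts, because every hospital has its control first.

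**3. Hospital days (all inputs assumed).** Patients admitted directly to ICU stay 5 days longer; their share shifts 3 or 5 points; SD is 6 days; n = 1,440 per period at one hospital.

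- artefact = 0.03 × 5 = 0.15 days, or 0.05 × 5 = 0.25 days
- naive SE = 6 × √(2/1440) = 0.224 days; 95% half-width = 1.96 × 0.224 = 0.44 days
- ratio to SE = 0.67 or 1.12
- chance that the 95% interval excludes zero with no true effect = Φ(ratio − 1.96) + Φ(−ratio − 1.96) = about 10% or 20%, instead of 5%

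The same artefacts with other sample sizes:

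| n per period | SE (days) | Chance at 0.15 days | Chance at 0.25 days |
|---|---|---|---|
| 1,000 | 0.268 | 9% | 15% |
| 1,440 | 0.224 | 10% | 20% |
| 3,000 | 0.155 | 16% | 36% |

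**4. Any ICU admission (assumed).** A patient admitted directly to ICU has the outcome by definition; the others have it with risk r. The artefact is shift × (1 − r).

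| r | 3-point shift | 5-point shift |
|---|---|---|
| 5% | 2.85 points | 4.75 points |
| 10% | 2.7 points | 4.5 points |
| 20% | 2.4 points | 4.0 points |

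The artefact is therefore less than the full shift whenever any other patient later enters ICU.

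**The case against.** **Other terms are modelled.** A reader might infer that age, sex and race are the only adjustment. They are not: the protocol model has period, site and their interaction, and SAP section 10 has hospital, study period and calendar time. What stands is narrower: no patient-level covariate beyond demographics is named, and period terms cannot help within one hospital.

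**The protocol's model may already cover these outcomes.** It is written for outcome in general, protocol section 9.4.1.2 lists hospital days, death and ICU admission as endpoints, and the SAP does not withdraw it. Even so, its declared purpose is to explore site heterogeneity, and SAP section 13 does not carry it over.

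**Severity data are not stated to be available.** This is correct. No severity score, admission type or present-on-admission flag is listed. Hospitalisation in the last 90 days is a field on the pharmacist intervention form, so it is missing for the control year and for admissions without an intervention. Bed-flow and ADT files can supply proxies such as first bed location, but no more should be claimed.

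**The crossover handles season.** It does so for a balanced pooled comparison of the two strategies. That analysis is optional, and the documents choose site-by-site evaluation.

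**The limitation is disclosed and secondary.** Both documents call the study essentially non-randomised and expect no definitive secondary findings. Disclosure limits the harm, but the data for a partial correction are already received.

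**Conclusion.** The plan concedes possible imbalance, adjusts for demographics alone where it models, and specifies only crude differences for hospital days and ICU admission, with no contrast for death. Case-mix shifts enter the site-specific and historical contrasts in full.

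The size cannot be derived from the documents. On the assumed inputs above it is 0.15 to 0.25 hospital days, roughly 0.7 to 1.1 naive standard errors at 1,440 per period. That lies inside the 95% half-width, but it is enough to raise the false-positive rate from 5% to about 10% to 20%.

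Two stronger readings are not supported. The documents do not show that case-mix did shift; they expect similar populations in the two periods. Nor does every strategy contrast inherit the bias: a shift common to all four hospitals leaves the balanced pooled comparison of strategies unbiased. The primary feasibility endpoints are descriptive, measured at hospital level and unaffected. This is a worthwhile correction to the secondary analyses and does not threaten the study's main purpose.

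**What to change.** 1. In SAP section 13, fit the protocol's covariate-adjusted model for hospital days and death, and add a death contrast to Table 3.
2. Add first bed location at arrival (ICU, ward or surgical, from bed flow) to these models and to the SAP section 10 DOT models. Use location at arrival, not any unit on day one, because under Strategy 1 the pharmacist can act on the first day.
3. Report unadjusted differences beside adjusted ones.
4. Do not adjust any-ICU admission for first location, since a first bed in ICU is itself the outcome. Analyse later ICU admission among patients not admitted directly to ICU, alongside the crude any-ICU difference.
5. Use admission type only if the ADT files contain it.
6. Use same-hospital admission in the prior 90 days only as a sensitivity covariate. Look-back is missing at the start of the historical year. With period 1 ending on 3 April and period 2 starting on 4 May, look-back reaches into the other strategy's period until about 2 July.
7. Keep discharge diagnosis codes out of the main model, since they can reflect events after the strategy has acted.

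The cost is modest programming from files already received. Only measured case-mix is controlled: first bed location is a coarse proxy and will not capture, for example, a seasonal change in infection type.

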#### 9.4.2 Data Acquisition

Cost and feasibility data will be obtained using hospital cost data (antibiotics and pharmacy FTE), questionnaires, and notes/observations created during interactions with hospital personnel. Patient endpoint data will be obtained from electronic pharmacy antibiotic prescribing data (start and stop dates for all antibiotics) and hospital databases (e.g., ADT data for admit/discharge dates for all patients; patient status database (mortality); and diagnosis code databases).

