### 3.1.3 Secondary Objectives

To estimate and compare the time required of the pharmacist to administer each strategy

1. To estimate and compare the resource utilization of each strategy, where resource utilization includes pharmacist time and cost of antibiotics.
2. To compare the days of therapy (DOT) for antibiotics of interest between each strategy  
DOT will be measured as the number of days a patient receives each targeted and alternative antibiotic during the hospital admission.
3. To compare patient-specific outcomes between each strategy, including but not limited to the following:
  - a. Total hospital days
  - b. Death
  - c. Intensive care unit admission
4. To compare the prescriber and pharmacist perceptions of the two stewardship strategies
5. To develop integrated measures of benefit: risk for AS (based on days of therapy, hospital days, and patient outcomes such as ICU admission and survival) and compare strategy effects with respect to these measures

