### 4.1 Study Population

#### 4.1.1 Selection of the Study Population

Four community hospitals in the Duke Infection Control Outreach Network (DICON) will be recruited for this study. Ideally, hospitals will have no teaching affiliation, bed size <300, and no existing antimicrobial formulary restriction and preauthorization or PAR practices in place at study start.

Drug use Identification: All study hospitals will have electronic systems that track antimicrobial prescriptions through orders, electronic medication administration records (eMAR), bar-coded medication administration (BCMA), or dispensing data.

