Stewardship Strategy 1 – Antimicrobial restriction and Pre-authorization. Following approval of the protocol at study hospitals, all prescriptions for targeted antibiotics will require phone approval by the trained PharmD. Prescribers will be instructed to discuss the patient details and the rationale for the desired antimicrobial with the PharmD. Specifically, prescribers must contact the pharmacist via pager or phone call to discuss the rationale for using the targeted antibiotic. The pharmacist will discuss the rationale and the specific clinical scenario with the prescriber and will decide if the targeted antibiotic is approved or denied. If the pharmacist denies the use of the targeted antibiotic, the pharmacist will provide recommendations for alternative antibiotics for the specific clinical scenario. The pharmacist will then document this interaction in the REDCap database, documenting which targeted antibiotic was requested, the prescriber’s rationale for requesting the targeted antibiotic, the patient’s symptoms and pertinent

clinical data at the time of the request, whether the request met the criteria for use of the targeted antibiotic (or not), and the pharmacist's recommendation. Prescriptions for targeted antibiotics will be eligible for intervention if written between 7am and 6pm Monday through Friday. Off-hours prescriptions will be reviewed for approval for continuation the following morning.

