2. Pharmacist time forms - These REDCap forms will be completed by the pharmacist at each hospital and will provide information concerning the time spent on the interventions.
3. Hospital level forms - These REDCap forms will be completed by DASON personnel. These data will include information regarding the approval and implementation of the stewardship strategies at each hospital
4. Questionnaires - These REDCap questionnaires will be completed by the pharmacists and prescribers at each hospital after each strategy is completed (at the end of the six month period). Pharmacists and prescribers will be sent a link to the questionnaires in order to complete. These will not require a REDCap account.
5. Pharmacy data - Antimicrobial utilization data are sent to Duke DASON from each of the study hospitals through routine DASON activities. These data will include PHI such as MRN and dates. These data are created through routine hospital pharmacy activities. These data files will include PHI such as MRN and dates. These data will be transmitted to DUHS via the same sFTP established for routine transmission of data described above. MRN data will not be included in the transfers to DCRI.
6. Bed Flow and Admission-Discharge-Transfer (ADT) data – We will receive bed flow (patient movement within the hospital) and ADT files from study hospitals on a monthly basis through standard DASON activities. These data files will include PHI such as MRN and dates. These data will be transmitted to DUHS via the same sFTP established for routine transmission of data described above. MRN data will not be included in the transfers to DCRI.
7. Demographics data - We will receive data from study hospitals on a monthly basis through standard DASON activities. These data files will include PHI such as MRN and dates. These data will be transmitted to DUHS via the same sFTP established for routine transmission of data described above. MRN data will not be included in the transfers to DCRI.
8. Billing/ICD-9 data - We will receive data from study hospitals on a monthly basis through standard DASON activities. These data files will include PHI such as MRN and dates. These data will be transmitted to DUHS via the same sFTP established for routine transmission of data described above. MRN data will not be included in the transfers to DCRI.

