408         than one intervention over the course of a year)

409 Signs and symptoms

410     • Fever

411     • Leukocytosis

412     • Hypotension

413     • Cough or Sputum production

414     • Other signs or symptoms

- 415 • List of other/specifies
- 416 • Number of signs and symptoms per intervention

417 Culture data

- 418 • Culture data available for review (yes/no)
- 419 • If yes, was the culture data reviewed
- 420 • If yes, did it help inform the recommendation?

421 Intervention outcome

- 422 • Was the recommendation followed?
- 423 • Was there an ID consult after the intervention?
- 424 • ICU admission

425 Ultimate Infection diagnosis related to recommendation

- 426 • Pneumonia
- 427 • UTI
- 428 • Meningitis
- 429 • Surgical site infection
- 430 • SSTI
- 431 • Colitis
- 432 • Bacteremia
- 433 • Sepsis with unknown source
- 434 • No infection
- 435 • Other
- 436 • List of other, specify

437 **10. Days Of Therapy**

438 **Purpose:** To address Secondary objective 2, to compare DOT for antibiotics of interest between each  
439 strategy.

440

- 441 • Days of therapy (DOT) for targeted and alternative antibiotics
  - 442 ○ Per the protocol, DOT will be measured as the number of days a patient receives
  - 443 each targeted and alternative antibiotic during the hospital admission

444 The three targeted antibiotics are:

- 445 • Anti-pseudomonal carbapenem of choice at the study hospital
- 446 • Vancomycin
- 447 • Piperacillin-tazobactam.

448 The alternative antimicrobials of interest are:

- 449 • Fluoroquinolones
- 450 • Cephalosporins
- 451 • anti-MRSA systemic antimicrobials (e.g., nafcillin, daptomycin, linezolid, ceftaroline,
- 452 clindamycin, and TMP-SMX).

Among admissions with an included antibiotic, by hospital

- Table 1
  - Year prior to study
  - Period 1 Admission with Included antibiotic, no intervention
  - Period 1 Admission with stewardship intervention
  - Period 2 admission with Included antibiotic, no intervention
  - Period 2 admission with stewardship intervention
- Table 2
  - Period 1 (all admissions with an antibiotic of interest)
  - Period 2 (all admissions with an antibiotic of interest)
- Table 3
  - For 3 contrasts (PAR vs Historical year; Res/PreA vs historical Year; PAR vs Res/PreA)
  - Difference in proportion used drug with 95%CI
  - Difference in Mean DOT with 95% CI

For each antibiotic,

- proportion of admissions where the antibiotic was received
- DOT for the antibiotic

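### Days of therapy is defined by drug received but sourced from prescribing dates, so it may include drug never given, possibly only in the preauthorization period

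*Combined protocol and SAP*

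**What the plan says.** **Definition.** Protocol 3.1.3 states: "DOT will be measured as the number of days a patient receives each targeted and alternative antibiotic during the hospital admission". SAP 10 repeats this and adds: "Admissions where the antibiotic was not received will have a DOT of 0". The companion outcome in SAP 10 is the proportion of admissions in which the drug was received.

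**Source.** Protocol 9.4.2 says that patient endpoint data come from "electronic pharmacy antibiotic prescribing data (start and stop dates for all antibiotics", together with hospital databases. Under protocol 4.1.1 a hospital may track use through "orders, electronic medication administration records (eMAR), bar-coded medication administration (BCMA), or dispensing data". The pharmacy item in protocol 16.2 reads: "Antimicrobial utilization data are sent to Duke DASON from each of the study hospitals through routine DASON activities". It does not say whether those records are orders, dispensings or administrations.

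**Strategy 1.** Under protocol 4.1.4, prescriptions for targeted drugs written on weekdays between 7am and 6pm are eligible for intervention. The pharmacist "will decide if the targeted antibiotic is approved or denied" and documents the exchange in REDCap. Off-hours prescriptions are reviewed the next morning for continuation. Strategy 2 reviews patients who have already had the drug for about 72 hours.

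**The concern.** The endpoint is exposure, and the named source is prescribing. A prescription with a start and a stop date shows that a drug was ordered over a span, not that a dose was given on each day of it, or at all. Protocol 9.4.1.2 lists days of use and prescriptions as separate endpoints, so the plan itself treats them as different quantities.

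The gap need not be equal across periods. Preauthorization can act before the first dose. Audit and feedback acts about three days in, and the historical year had neither. If a denied prescription leaves a dated record that is then counted, the error falls in the preauthorization period alone. It would understate that strategy's effect against the historical year and against audit and feedback. Hypotheses 4 to 6 rest on these contrasts, and hypothesis 6 expects preauthorization to be the weaker strategy.

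The choice of record also decides which admissions count as having an included antibiotic, which is the analysis set in SAP 10 and 13.

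**Working it through.** **1. Passages side by side**

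| Question | What the documents give |
|---|---|
| What is a day of therapy? | A day on which the patient receives the drug (protocol 3.1.3, SAP 10) |
| What if nothing is received? | DOT is 0 (SAP 10) |
| Which record shows receipt? | Prescribing start and stop dates (protocol 9.4.2); orders, eMAR, BCMA or dispensing are all accepted (4.1.1) |
| How are first and last days counted? | Not stated |
| How are denied, cancelled or never-given orders handled? | Not stated |
| Must the source match across hospitals or periods? | Not stated |

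Of the four accepted systems, eMAR and BCMA record administration; orders and dispensing do not. The zero rule says what DOT should be when no drug is received, not how start and stop dates would reveal it.

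**2. The plan's own figure**

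Protocol 9.1 gives 97% power within a hospital for a difference of 0.05 (example: the proportion with zero DOT), with 0.50 in one group, 3000 patients per period and alpha 0.05. Sidedness is not stated; I take it as two-sided.

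Power = Φ[(d − 1.96·SE0) / SE1], with SE0 = √(2·p̄(1−p̄)/n) and SE1 = √((p1(1−p1)+p2(1−p2))/n).

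For p1 = 0.50, p2 = 0.55 and n = 3000: SE0 = 0.01289, SE1 = 0.01288, and power = Φ[(0.05 − 0.02527)/0.01288] = Φ(1.92) = 97.3%. The stated figure reproduces.

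**3. Error in the preauthorization period only (illustration)**

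Assume that zero DOT is truly 0.50 in the comparator and 0.55 under preauthorization, and that a share m of the 5 averted points is recorded as DOT above zero. The recorded proportion is 0.55 − 0.05m.

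| m (assumed) | Recorded difference | Power |
|---|---|---|
| 0 | 0.050 | 97.3% |
| 10% | 0.045 | 93.7% |
| 25% | 0.0375 | 82.8% |
| 50% | 0.025 | 49.1% |
| 75% | 0.0125 | 16.1% |
| 100% | 0 | no difference |

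The loss of power reflects a bias of 0.05m, which more patients would not remove.

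**4. Equal error in both periods**

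If a share f of true zeros is misrecorded in both periods, the difference is 0.05(1 − f). For f = 2%, 5% and 10% it is 0.049, 0.0475 and 0.045, with power 96.7%, 95.7% and 93.7%. Small common error matters little.

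**5. Bounding case**

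Suppose a share d of targeted orders is denied before a dose, and every denial leaves one counted order-day. The recorded reduction in the proportion using the drug is then 0 where the true reduction is d, and d days are added per ordered admission. With d assumed at 10–20%, that is 0.1–0.2 DOT. For mean DOT the distortion is smaller: if a denial averts a course of L days, only 1 of the L days is lost from the recorded effect.

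**The case against.** The strongest reply is that the documents nowhere show a denied request being counted. Strategy 1 has the prescriber phone or page, and the trace that the protocol describes is a REDCap form. Nothing says that a denied request becomes a dated pharmacy record, and the SAP sets DOT to zero when the drug is not received. A reader might infer that the plan counts denied orders as therapy and so builds in a result that favours hypothesis 6. The text does not support that. It leaves the matter open, and some sites may already supply administration data.

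Other parts of the reply also stand:

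- Off-hours prescriptions reviewed for continuation may already have been given. Those days would be true DOT.
- In-hours cover is 11 × 5 = 55 of 168 hours, or 33% of the week. If prescriptions were spread evenly (an assumption), pre-dose denial of 10–20% of all targeted orders would need 31–61% denial in those hours; if half were written in hours, 20–40%. The bounding case is therefore demanding.
- An open order span that covers days without a dose, as with intermittent dosing, would occur in all three periods. It inflates the level of DOT but is not evidence of bias between strategies.
- Sites are evaluated separately and pooling is optional, so a source held constant within a hospital largely cancels common error.

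What the reply does not remove is the mismatch between definition and named source. Nor does a constant source cancel error that arises only from denials.

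**Conclusion.** The point holds as a mismatch between the stated endpoint and the stated source, not as proof of miscounting. Computed from prescribing dates, DOT and the proportion using a drug may include orders or days with no drug given. Where a targeted prescription is written and then denied before a dose, the error may be confined to preauthorization and would understate its effect in two of the three contrasts.

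The size cannot be fixed from the documents, which give neither a denial rate nor each hospital's record type. Under the assumptions shown, the recorded effect ranges from nearly intact (a tenth misrecorded) to half lost (half misrecorded). Complete loss is only the bounding case in which every pre-dose denial is counted.

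The primary feasibility endpoints are unaffected. The change is still worth making, because DOT is secondary objective 2 and heads a planned report in SAP 1.

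**What to change.** In protocol 9.4.2 and SAP 10:

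- Derive DOT and the proportion using each drug from calendar days with at least one documented administration (eMAR or BCMA), wherever a hospital has these records.
- Use the same source and day-counting rule in that hospital's historical year and both strategy periods.
- Where only orders or dispensing exist, apply one identical rule for cancelled or never-dispensed orders to all three periods. Do not remove denied orders from Strategy 1 alone: that would bias the contrast the other way, and the REDCap items described include no field for whether a dose was given.
- Flag DOT from such a site, and show any pooled estimate with and without it as a sensitivity analysis.
- List the source type by hospital, for instance among the hospital listings in SAP 4.

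The cost is SAP wording and some extra derivation work. The documents do not show which of the four hospitals hold administration records, so the sensitivity analysis may rest on fewer sites.
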